#### Qualitative interviews

Qualitative interviews occur pre-intervention and post-intervention with a subset of partnered yoga participants to explore the impact of cLBP and comorbid mental health disorders on family and marital processes. This will also provide a greater detailed understanding of yoga's perceived impact of on the Veteran and possibly the Veteran’s family. After randomization, a purposive sample of partnered Veterans (*n* = 20 couples) in the yoga arm are recruited to participate. To be eligible for interviews, Veterans must report having a cohabitating or long-term committed partner/spouse. In addition, both the Veteran and the Veteran’s partner must give consent to participate in the interviews. Sampling takes place in a logistically feasible way until the goal sample size is reached.

Separate and conjoint interviews are conducted by a trained qualitative interviewer with the Veteran and his or her partner at two time points – prior to participation in yoga and approximately four weeks after ending classes – in order to maximize the opportunity to authentically discuss the impact of cLBP and yoga on family relationships. Interviews are conducted with each member of the couple individually followed by a short conjoint interview. We encourage couples to attend interviews at the same time. However, if this is not possible, we conduct the two interviews within approximately 72 hours. Semistructured interview guides incorporate the following domains: the Veteran’s perception of the impact of cLBP on himself or herself and the partner or family in terms of mood and functioning; the partner’s perception of the impact of the Veteran’s cLBP on the Veteran’s mood and functioning; the partner’s perception of the Veteran’s cLBP on her/his own and overall family mood and functioning; the attitude of the Veteran and partner toward yoga; the Veteran and partner’s perception of change in the Veteran’s cLBP; the Veteran and partner’s perception of any possible change in psychological concerns including PTSS, depression, and anxiety after yoga; and the Veteran and partner’s perception of any change in overall family mood and functioning after yoga classes (see Additional file 4).

Interviewers obtain informed consent from the Veteran and partner prior to the interviews. Each individual receives $25 for each 60–90 minute interview visit. Interviews take place at a location convenient to the couple.

If a couple completes a pre-intervention interview but declines to complete a second interview, we attempt to replace that couple with another couple.

### Adverse events and data monitoring

The same strategy for collecting adverse event data is implemented for both study arms. Participants are instructed at enrollment to contact research staff immediately if they experience any adverse event during the study. All participants have 24-hour emergency contact information for the site investigator and another member of the research team. All post-baseline surveys and education check-in calls include questions on whether the Veteran believes he or she has incurred any possible adverse events. Veterans in the yoga group are given the opportunity to speak with a research staff member regarding any potential adverse events during attendance and check-ins at yoga classes. Research staff and the principal investigator follow up on all adverse event reports as appropriate. Unanticipated problems (unexpected, related, and serious) are reported to the IRBs and sponsor within 48 hours.

A Data and Safety Monitoring Board (DSMB) reviews the study conduct and results throughout recruitment, data collection, and treatment implementation phases. The DSMB is composed of four members who are not involved in the conduct of the study. The DSMB meets semiannually throughout the study period to review all adverse event reports, accrual progress, and retention. A summary report of the board’s findings and recommendations are submitted to the sponsor and IRBs.

This study will be stopped prior to its completion if: (1) the intervention(s) are associated with adverse effects that significantly impact the risk-benefit ratio; (2) study recruitment or retention becomes futile; (3) any new information becomes available during the trial that necessitates stopping the trial; or (4) other situations occur that might warrant stopping the trial.

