Yoga classes contain no more than eight to ten Veterans and two yoga teachers to assure a low Veteran-to-instructor ratio (no more than five Veterans to one teacher). This arrangement maximizes effectiveness and safety, and allows flexibility in yoga teacher scheduling based on the study’s needs. Veterans are asked to attend one 75-minute class per week and receive reminder phone calls the day before each scheduled class. Attendance is taken by research staff. We provide $10 travel compensation for each yoga session. Mats and props are provided. Each class includes a yoga breathing exercise (*pranayama*), discussion of yoga philosophical principles, yoga postures (*asanas*), and a relaxation exercise (*svasana*). Veterans are frequently advised to proceed carefully and slowly. The difficulty of postures increases throughout the 12 weeks (Table 2). The 12-week intervention period is divided into four 3-week segments, titled Opening to Something New, Listening to Your Back, Engaging Your Power, and Bringing it Home. Posture variations, modifications, and various aids (e.g., block, chair, strap, wall) are built into the protocol to accommodate a range of abilities. Yoga participants are encouraged to practice at home for 30 minutes on days when they do not have class. To help Veterans practice at home, they receive a guidebook describing and depicting the protocol (see Additional file 1), yoga mat, strap, two blocks, and home practice instructional videos (see Additional file 2-5). Home practice videos portray Veterans in an introductory video describing the value of yoga practice in their own lives, two 30-minute videos that follow the same structure as group yoga classes, and one 20-minute extended breathing and relaxation video. Veterans are given a link to view the home practice videos online or, if requested, they receive a take-home DVD.

**Table 2 Tab2:** Twelve-week standardized hatha yoga protocol

Yoga posture (*asana)* or class component	Classes incorporating component by segment			
	Segment 1	Segment 2	Segment 3	Segment 4
	Weeks 1–3	Weeks 4–6	Weeks 7–9	Weeks 10–12
	Opening to Something New	Listening to Your Back	Engaging Your Power	Bringing it Home
Breathing exercise	✓	✓	✓	✓
Knees to chest pose^*^	✓	✓	✓	✓
Knees together twist pose	✓	✓	✓	✓
Pelvic tilt pose^*^	✓			
Big toe pose^*^		✓	✓	✓
Cat and cow pose*	✓		✓	
Wheel pose^*^	✓		✓	
Chair pose^*^	✓	✓	✓	
Shoulder openers^*^	✓	✓	✓	✓
Crescent moon pose^*^	✓	✓		✓
Mountain pose^*^	✓	✓	✓	✓

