#### Education

*The Back Pain Helpbook* [68] is given to individuals randomized to the education group. This book has been used successfully in previous cLBP studies for educational purposes [32, 80]. The book includes information on how back pain is influenced by posture, emotions, fear avoidance behaviors, and social support. It also encourages pain self-management strategies such as mind-body relaxation techniques, exercise programs, and medications. In addition, Veterans receive a handout after randomization suggesting specific chapters to read throughout the intervention period and brief mailed newsletters every three weeks that highlight main points from the recommended chapters (see Additional file 7). Check-in calls, which are proceeded by a newsletter mailing, are conducted by research staff every three weeks to assess progress and reinforce study retention efforts.

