### Data collection

Outcome data are collected at baseline, 6 weeks, 12 weeks, and 24 weeks. Participants in both treatment arms complete paper surveys in person and receive cash honoraria after the completion of each survey. We give $25 at baseline, 6 weeks, and 12 weeks. At the final follow-up at 24 weeks, participants receive $50 after completion of their survey. Paper surveys are double-entered into StudyTRAX™ by research staff who have no knowledge of or access to identifiable participant information or treatment assignment. The two data entries are compared and reconciled.

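### Adverse-event collection is described as the same in both arms, but contacts between surveys differ in mode and frequency, so all-source counts by arm are open to ascertainment bias of unknown direction

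*Protocol article*

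**What the plan says.** All statements are in the protocol article.

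- **Principle** (Adverse events and data monitoring): "The same strategy for collecting adverse event data is implemented for both study arms".
- **Spontaneous route, both arms** (same section): "Participants are instructed at enrollment to contact research staff immediately if they experience any adverse event during the study". All participants also hold round-the-clock emergency contact details.
- **Direct questions** (same section): "All post-baseline surveys and education check-in calls include questions on whether the Veteran believes he or she has incurred any possible adverse events". The surveys cover both arms; the calls are for education only.
- **Yoga route between surveys** (same section): "Veterans in the yoga group are given the opportunity to speak with a research staff member regarding any potential adverse events during attendance and check-ins". The setting is the weekly class.
- **Call frequency** (Education): the calls "are conducted by research staff every three weeks to assess progress and reinforce study retention efforts".
- **Class frequency** (Hatha yoga): "Veterans are asked to attend one 75-minute class per week and receive reminder phone calls the day before each scheduled class".
- **Survey times** (Data collection): "Outcome data are collected at baseline, 6 weeks, 12 weeks, and 24 weeks".

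Safety belongs to the overall goal in the opening statement of Specific aims. Adverse effects are also the first of the listed grounds for stopping the study early, and the DSMB reviews every adverse event report.

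**The concern.** The paragraph claims a property, equal collection, and then describes contacts that lack it. Between surveys, one arm is asked and the other is offered a chance to speak. The number of contacts differs as well, and the yoga route depends on coming to class. A yoga Veteran who stops attending loses that route, whereas an education Veteran who stops reading the book is still scheduled for calls.

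What is at stake is the reading of adverse-event counts by arm. Anyone who relies on the stated principle, including those who monitor the study, would take a difference in all-source counts as a difference in events. Part of it, or part of an absence of difference, could come from how events were elicited. An analysis cannot make unequal collection equal afterwards; it can only restrict the comparison to what was collected alike. The efficacy endpoints are not affected.

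**Working it through.** The plan states no figure on this point, so there is none to reproduce. The check is a count of scheduled contacts, followed by an illustration of what unequal contacts could do.

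**Step 1: count the contacts.** I assume that the check-in calls run over the 12-week intervention period, since the Education section ties the reading plan to that period.

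- Education calls: 12 weeks ÷ 3 weeks = 4.
- Yoga classes: 12 weeks × 1 per week = up to 12, or 9 at the attendance threshold for the per-protocol analysis (Primary outcome analyses).
- Post-baseline surveys: weeks 6, 12 and 24, so 3 in each arm, 2 of them by week 12.

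| Scheduled route | Education | Yoga |
|---|---|---|
| Direct questions by week 12 | 4 + 2 = 6 | 2 |
| Direct questions by week 24 | 4 + 3 = 7 | 3 |
| Opportunity to speak at class | 0 | up to 12 |
| Instruction to report at once | yes | yes |

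If the calls fall in weeks 3, 6, 9 and 12, two of them coincide with surveys. Direct questioning by week 12 then happens at 4 distinct times in education and at 2 in yoga.

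**Step 2: illustrate the effect.** The reporting probabilities below are assumptions; the document gives none. Let q be the chance of reporting an event when asked, o the chance of volunteering it at a class, and a the attendance rate. Take an event in the 12-week period as detectable at the next call and next survey in education, and at the next survey and next two classes in yoga, with independent chances.

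- Education: D_E = 1 − (1 − q)²
- Yoga: D_Y = 1 − (1 − q)(1 − o·a)²

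With equal true event rates:

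| q | o | a | D_E | D_Y | D_Y / D_E |
|---|---|---|---|---|---|
| 0.5 | 0.05 | 0.75 | 0.75 | 0.54 | 0.72 |
| 0.5 | 0.20 | 1.00 | 0.75 | 0.68 | 0.91 |
| 0.5 | 0.60 | 1.00 | 0.75 | 0.92 | 1.23 |
| 0.7 | 0.05 | 0.75 | 0.91 | 0.72 | 0.79 |
| 0.7 | 0.60 | 1.00 | 0.91 | 0.95 | 1.05 |
| 0.9 | 0.05 | 0.75 | 0.99 | 0.91 | 0.92 |
| 0.9 | 0.60 | 1.00 | 0.99 | 0.98 | 0.99 |

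For q from 0.5 to 0.9, o from 0.05 to 0.6 and a from 0.75 to 1, the ratio runs from about 0.72 to 1.23.

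**Step 3: where the sign changes.** The arms detect equally when (1 − o·a)² = 1 − q, that is o·a = 1 − √(1 − q). This gives 0.29 for q = 0.5, 0.45 for q = 0.7 and 0.68 for q = 0.9. Below these values yoga is under-counted relative to education; above them it is over-counted. Nothing in the article says on which side the trial lies.

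**The case against.** The strongest reply is that most of the structure is common. Both arms answer direct adverse-event questions in person at weeks 6, 12 and 24, and both are told to report at once. A reader might infer that yoga Veterans are never asked about adverse events. That is wrong: the lack of a stated question applies only to contacts between surveys. This part of the reply stands.

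Second, a reader might infer that the safety comparison is biased, perhaps in favor of yoga, or distorted by a large multiple. The documents support neither. Yoga has up to 12 face-to-face contacts against about 4 calls, so frequency may offset the weaker mode or more than offset it. Any multiple taken from the calls and classes alone also leaves out the common surveys. This stands too and limits the conclusion to openness to bias.

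Third, the article is condensed. It does not say that the calls follow a script, and it does not rule out that staff put a question at the class check-ins; a manual may cover that. If so, the gap in mode narrows, but frequency and dependence on attendance still differ, and the published description still needs correcting.

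Fourth, non-attenders are not out of reach. The surveys do not depend on attendance, yoga Veterans get a reminder call before each class, and attendance is reviewed regularly. However, no adverse-event question is attached to those reminder calls.

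Finally, the article plans no formal between-arm test of adverse events, and safety is not the subject of any of the four enumerated aims. That lowers the weight of the point. Even so, the opening statement of the aims calls for a safety conclusion, and counts by arm are likely to be read as comparable once collection has been called the same.

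**Conclusion.** The point holds in a limited form. The claim of one strategy is contradicted within its own paragraph, and no other section reconciles it. The firm part is the count: by week 12, about 6 scheduled direct inquiries in education against 2 in yoga, and up to 12 class opportunities in yoga against none in education. It rests on calls every three weeks for 12 weeks and on no question being stated for the classes.

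It follows that all-source adverse-event counts by arm are open to ascertainment bias of unknown direction and size. The range of 0.72 to 1.23 shows that either direction is possible; it depends entirely on assumed reporting probabilities and is not an estimate for this trial. The point is worth acting on because the remedy is cheap and a common source of data already exists. It does not threaten the primary efficacy conclusion.

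**What to change.** 1. Correct the sentence on a common strategy. State which routes are shared (surveys, spontaneous reports) and which are specific to an arm (calls, classes).
2. Base the between-arm adverse-event comparison on the survey questions asked of both arms at weeks 6, 12 and 24.
3. Report events from calls, classes and spontaneous contact separately, by arm and source, so that nothing is lost from the safety record.
4. Optional, for participants still to come, since the Trial status section says that recruitment is open: have the staff who already take attendance put the same adverse-event question to yoga Veterans every three weeks, with a call to anyone absent.

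**Cost.** Items 1 to 3 need wording and a small amount of analysis work. Fewer events enter the headline comparison, and that comparison depends on recall and on survey completion. Item 4 adds one question for staff already present and a few calls. Because it would start partway through the trial, it would improve capture for later participants without making the earlier class data comparable.

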### Data analysis

We will conduct both intention-to-treat and per-protocol analyses, with the intention-to-treat analysis being primary. Descriptive statistics including means, medians, and standard deviations for continuous variables, and the number and proportions for categorical variables will be reported. All analyses will be performed at the α = 0.05 level of significance.

The success of randomization will first be assessed. We will compare the two groups on baseline characteristics and demographics, including stratification variables, with Student’s t test or chi-square test, as appropriate, using an α = 0.1 level of significance. Variables that differ between the groups at baseline will be considered possible confounders and adjusted for in subsequent analyses.

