### Randomization

The baseline survey is typically completed within 45 days after eligibility screening. If the period since screening exceeds 45 days, eligibility is re-assessed and verified prior to the baseline survey. After completion of the baseline survey, the participant is randomized in a 1:1 ratio to yoga or education using StudyTRAX™ (Macon, GA), a HIPAA-compliant study management software platform. Permuted block randomization with varying block sizes of two or four is used. Stratification is done on three dichotomous variables to assure similar distribution between the two groups:Age (≤45, >45 years). Back pain in older Veterans may be structurally different. Furthermore, age may be a confounding variable to the response to yoga.PCL-C score (<30, ≥30). These cut-offs will help assure equivalent numbers of Veterans with PTSS in both treatment arms in order to compare the effectiveness of the interventions for reducing comorbid PTSS. PTSS may also be an effect modifier for yoga and cLBP.Partnered (yes/no). A partnered Veteran is defined as one who reports having a cohabitating or long-term committed partner/spouse. This helps assure adequate numbers of partnered Veterans in the yoga group available for qualitative interviews.

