#### Primary outcome analyses

The primary hypothesis is that 12 weeks of yoga will be more effective than education for improving pain and function. For both outcomes, we will determine if yoga is superior to education based on a longitudinal model incorporating all measurements across the study period, including baseline, week 6, week 12, and week 24. The primary hypothesis will be tested using a contrast of the change from baseline to week 12 comparing the two groups within this model. To account for correlation among repeated measures for the same individual, we will assume an unstructured covariance for the initial model. A simpler model may be used for the covariance if appropriate. No missing data will be replaced in these analyses, and all available data can be included. The analysis is considered to be unbiased under a missing-at-random assumption. It is possible that any missing data may be non-ignorably missing rather than missing-at-random. We will perform sensitivity analyses to determine if the results are robust to the missing data mechanism. Note that we require statistical significance for both outcomes rather than either outcome to address the issue of multiple testing. We will report mean differences between groups with standard errors, 95 % confidence intervals, and *p* values. If the analysis of the success of randomization finds any imbalance between groups, the above model will be adjusted for these factors.

Per-protocol analysis will also be conducted similarly. Adherence to the yoga protocol will be defined as attending at least 9 of the 12 yoga classes. For education, adherence will be defined as reading at least three-fourths of the book by self-report.

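### Baseline tests at α = 0.1 choose the covariates of the primary model, so the model is not fixed in advance and will almost never include the three randomisation factors

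*Protocol article*

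**What the plan says.** All references are to the protocol article.

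- **Data analysis.** Baseline characteristics are compared between arms, "including stratification variables, with Student’s t test or chi-square test, as appropriate, using an α = 0.1 level of significance". The consequence follows: "Variables that differ between the groups at baseline will be considered possible confounders and adjusted for in subsequent analyses".
- **Primary outcome analyses.** The model is longitudinal, with baseline and weeks 6, 12 and 24 all as measurements and an unstructured covariance to start with. "The primary hypothesis will be tested using a contrast of the change from baseline to week 12 comparing the two groups within this model". The section then brings in the baseline check: "If the analysis of the success of randomization finds any imbalance between groups, the above model will be adjusted for these factors".
- **Randomization.** "Stratification is done on three dichotomous variables to assure similar distribution between the two groups": age (≤45/>45), PCL-C (<30/≥30) and partnered (yes/no). "Permuted block randomization with varying block sizes of two or four is used". On age, the section remarks that "age may be a confounding variable to the response to yoga"; it also says that PTSS may modify the effect.

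No section names a covariate for the primary model, and none says that the randomisation factors enter whatever the baseline tests show. The one baseline covariate named in advance is baseline pain medication use, in the logistic regression for medication. PCL-C group and age group appear later as subsets for analysis, not as terms in the primary model.

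**The concern.** After proper randomisation, baseline differences arise by chance. A p-value below 0.1 therefore does not show that allocation failed, and it does not show that the variable predicts outcome. A rule built on it has three consequences.

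1. The covariates of the confirmatory model for both co-primary outcomes are unknown until baseline data have been examined by arm.
2. The rule works against the design. Blocking within strata is meant to balance the three factors, and balance is what keeps them from being flagged. The analysis then treats a stratified trial as if it were unstratified.
3. Baseline pain and baseline RMDQ are baseline characteristics and are also responses in the model. If one is flagged, the rule would enter it a second time, as a covariate for itself.

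Both co-primary outcomes must be significant, so any power lost on RMDQ, the weaker of the two at a planned 82%, lowers the chance that the trial succeeds.

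**Working it through.** **1. The plan's own power.** Inputs from the section on sample size: 120 randomised and 20% dropout, so 120 × 0.8 = 96 completers, 48 per arm; two-sided α = 0.05. For two means, the noncentrality is (difference / SD) × √(48/2).
- Pain: (2.0/2.5) × 4.899 = 3.92, power 97% (plan: 97%).
- RMDQ: (3.0/5.0) × 4.899 = 2.94, power 83% (plan: 82%).

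These reproduce as unadjusted comparisons of change scores and are not in dispute.

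**2. Chance flags.** For k independent unstratified variables tested at 0.1, P(at least one flag) = 1 − 0.9^k and the expected number is 0.1k. The article gives no count, so k is assumed.

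| k | P(at least one flag) | Expected flags |
|---|---|---|
| 10 | 65% | 1 |
| 15 | 79% | 1.5 |
| 20 | 88% | 2 |
| 30 | 96% | 3 |

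Correlation among the variables lowers the middle column. Baseline pain and RMDQ have about a 10% chance each, and at most 1 − 0.9² = 19% for either if independent.

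**3. Can a stratification factor be flagged?** With blocks of at most four, the arms differ by at most 2 within a stratum. One level of a factor spans four of the eight strata, so the arms differ by at most 8 within it. If each level holds 60 people, the worst table is 34/26 against 26/34. Its chi-square is 120 × (34² − 26²)² / 60⁴ = 2.13, below the 0.1 critical value of 2.71. Simulation gives the same picture: N = 120, 8 strata, blocks of 2 or 4, and 3,000 trials for each of three assumed prevalence patterns. None of the three dichotomous factors was flagged in any trial, against 10% to 12% per factor under simple randomisation. If age and PCL-C are tested as continuous scores, they are flagged in about 1% to 3% of trials.

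**4. What adjustment does in the planned model.** Write the four visits as the baseline value plus three changes from it. A factor entered as a main effect shifts every visit equally and drops out of the changes. With complete data and an unstructured covariance, the week-12 contrast is estimated from the changes alone, so the main effect alters neither the estimate nor its standard error. Direct fits confirm this. With 20% dropout at weeks 12 and 24, main effects lowered the mean standard error by less than 1% (1.033 to 1.026, and 1.070 to 1.060). Factor-by-visit terms instead let the changes depend on the factors. With complete data the contrast then equals a regression of change on arm and factors.

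**5. Size when the factors predict change.** Change-score regression for RMDQ: difference 3, SD 5 (0.6 SD), 96 completers, stratified blocks as above. The variance shares are assumptions.

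| Variance of change explained | Power without / with factors | Type I error without / with |
|---|---|---|
| 5% | 84% / 85% | 4.7% / about 5% |
| 10% | 84% / 87% | 4.3% / about 5% |
| 20% | 85% / 90% | 3.6% / about 5% |

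At 0% explained, leaving the factors out costs nothing. Repeat simulations agree to within about one percentage point.

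**6. A flagged baseline outcome.** If baseline RMDQ is both a response and a covariate, it predicts itself exactly at the baseline visit. The residual there can be made zero, and the unstructured covariance becomes singular.

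**The case against.** The strongest objection concerns the model. The primary test is a change-from-baseline contrast, and the article does not say that flagged variables enter with visit interactions. Entered as main effects, they barely move the contrast, whether they are randomisation factors or chance-flagged variables. This stands. The power and type I figures above apply only to adjustment of the change itself, and adding the three factors as main effects would not recover the power.

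Two stronger inferences are tempting. A reader might infer that choosing covariates by baseline tests inflates the false-positive rate. The calculations do not support that: type I error was at or below the nominal 5% whenever the factors were left out or the rule was applied. A reader might also take 88% or 96% as the chance that this trial's model is altered. The article gives no count of variables, and several measures (PCL-C, PHQ-9, GAD-7, PSQI) are likely to be correlated, so those figures are illustrative.

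The article also gives no prognostic strength for the factors. It says only that age and PTSS may matter, and it stratified on partner status to secure interview couples.

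A separate analysis plan could name covariates. But this is not a detail left open: the article states the rule and applies it to the primary model, so such a plan would have to override it.

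**Conclusion.** The concern holds as a matter of pre-specification and efficiency, not of validity. It should be fixed, but it does not undermine the trial's main inference.

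- **Certain from the text:** the covariates of the primary model depend on baseline tests at α = 0.1, and the randomisation factors have no route into the model except a test that stratified blocking almost always stops them from failing.
- **Dependent on assumptions:** how often some variable is flagged (65% to 96% for 10 to 30 independent variables) and how much power is lost. On RMDQ the loss is about 1, 3 and 5 percentage points if the factors explain 5%, 10% and 20% of the variance in change, and nothing if they explain none.
- **Direction:** without the factors the test is conservative.

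**What to change.** 1. Delete the rule that selects covariates by baseline tests, in both sections where it appears, and report the baseline table descriptively without p-values.
2. State that the primary longitudinal model for both co-primary outcomes, and the analogous secondary models, includes age group, PCL-C group and partner status, each with its interaction with visit.
3. Name now, on prognostic grounds, any further covariates. Baseline pain and RMDQ should not be among them for their own models while baseline remains a response.
4. Keep adjustment for observed imbalance only as a labelled sensitivity analysis.

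The cost is wording. The factors are already collected for randomisation, and the article reports that the trial is still recruiting, so the change can be made before outcome data by arm are seen. Three factors at four visits use 3 × 4 = 12 mean parameters in place of the 3 that main effects would need. If the factors are not prognostic, the loss of precision is negligible.
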